### Trial promotion and engagement

Because a previous similar study (the GACHE trial) was stopped early due to poor recruitment rates, we have put particular effort into maximising recruitment. This has included keeping the (NOTE) principal investigators, research nurses and the community engaged in the trial. The trial is being publicised regularly using the Encephalitis Society website and newsletter, social media, and patient journey articles. The Encephalitis Society are playing a key role in providing additional support to the patients and their families aside from their work for the trial. At the annual World Encephalitis Day we have engaged with clinicians, patients, families and the public to raise awareness of encephalitis and the trial, especially through social media, newspapers, radio and television. To promote site engagement, study days are arranged for research teams to attend, along with scheduled research nurse teleconferences to allow ideas on maximising recruitment and updates on trial progress to be shared. Research investigators are invoted to the annual Neurological Infectious Diseases course in Liverpool^45^ Sites are also kept updated through our website (www.dexenceph.org.uk), and newsletters. In addition we use an innovative sticker chart, whereby a sticker is sent out to every site each time a patient is recruited anywhere in the country, approximately once a month (figure 2); this helps keep the study at the forefront of investigators minds. In addition, in case the DexEnceph study did not recrut to target a parralele study was set up by French colleagues, using the same protocol, so that data could be pooled if needed.

**Figure 2 F2:**
[figure not shown]
DexEnceph sticker chart.

### Trial closure

The end of the trial is defined to be the date on which data for all participants is frozen and data entry privileges are withdrawn from the trial database. The trial may be closed prematurely by the trial steering committee, on the recommendation of the IDSMC if there is sufficient evidence of risk to patient safety.

### Pharmacovigilance

Oversight of the trial is provided by the trial steering committee, which meets at least annually to review trial progress, safety, and adverse events (AEs). The committee is also informed of any protocol changes by the clinical trial research unit.

The Medicines for Human Use (Clinical Trials) Regulations 2004 (SI 2004/1031) definitions are used for AE, adverse reaction (AR), unexpected AR, serious AE (SAE), serious AR (SAR) or suspected unexpected SAR(SUSAR).

Depending on the nature of the event the reporting procedures below are followed:

SAEs occurring up to 30 days after randomisation are reported through an SAE Form (if serious) or in the 30 days/discharge case record forms (CRF) if they are a notable event (positive PCR in CSF at second lumbar puncture, gastrointestinal bleed, hyperglycaemia requiring change in medical management, opportunistic infections, unexpected/severe neuropsychiatric events).SAEs occurring after 30 days from randomisation are monitored through reporting in the CRFs with safety data collected in the 26 weeks and 78 weeks CRFs if serious.

The research investigator at each study site (or designated other) assesses all AEs for seriousness, causality and severity. The chief investigator (or designated other) assesses all adverse drug reactions for expectedness from known side effects of the use of dexamethasone.^46^ All serious ARs, AEs and SUSARs occurring up to 30 days from randomisation (apart from death unless the investigator suspects causality) require reporting to the clinical trials unit, within 24 hours of the site becoming aware of the event. In the case of death of a patient causality will be assessed by the trial steering committee.

The clinical trials unit will notify the Medicines and Healthcare products Regulatory Agency and main research ethics committee of all SUSARs that occur during the study according to the following timelines; fatal and life-threatening within 7 days of notification and non-life-threatening within 15 days. All investigators are informed of all SUSARs occurring throughout the study.

SAEs occurring after 30 days from randomisation are monitored by the clinical trials unit via the 26 weeks and 78 weeks CRFs. These CRFs need to be received at the clinical trials research unit by 4 weeks after the 26 and 6 weeks after 78 weeks time points.

Safety data are provided to the IDSMC, who are responsible for safeguarding the interests of trial participants and assessing the safety of the interventions during the trial; the IDSMC ensures action is taken as needed should they become aware of trends in reported AEs that raise safety concerns.

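### The duty to notify every SUSAR during the study has no prompt route behind it after day 30, and two parties are given causality of deaths

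*Protocol article*

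**What the plan says.** All of the main statements stand in the Pharmacovigilance section of the protocol article.

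- **Prompt reporting.** The rule covers "All serious ARs, AEs and SUSARs occurring up to 30 days from randomisation". These go to the trials unit within 24 hours of the site learning of them. Death is carved out, "apart from death unless the investigator suspects causality".
- **After day 30.** The section names one route, twice: "SAEs occurring after 30 days from randomisation are monitored through reporting in the CRFs", and again "SAEs occurring after 30 days from randomisation are monitored by the clinical trials unit via the 26 weeks and 78 weeks CRFs". Those forms must arrive by 4 weeks after the 26-week point and 6 weeks after the 78-week point.
- **Onward notification.** The trials unit notifies the regulator and the ethics committee of "all SUSARs that occur during the study according to the following timelines; fatal and life-threatening within 7 days of notification", and of non-life-threatening ones within 15 days.
- **Causality.** The site investigator, or a designee, judges causality of all adverse events. For deaths, however, the section states: "In the case of death of a patient causality will be assessed by the trial steering committee". The only meeting frequency given for that committee is that it is a body "which meets at least annually to review trial progress, safety, and adverse events".

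Elsewhere, the Data capture methods section asks for completed forms to be returned within 7 days of completion.

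**The concern.** The onward duty covers the whole study, but the reporting rule that feeds it stops at day 30. A SUSAR is a kind of SAE, so a late one follows the route that the section gives for late SAEs: a scheduled visit form. The trials unit cannot notify what it has not received, and the data monitoring committee cannot act on it.

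The second problem is the trigger for deaths. Up to day 30, whether a death is reported within 24 hours depends on the investigator's suspicion. The section then assigns causality of deaths to the steering committee and does not say how the two judgements relate. If the investigator does not suspect a link, the 24-hour rule does not apply, and the section sets no time by which the committee must learn of the death.

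The stake is the trial's own safety question. The Introduction says that immunosuppression could in theory favour viral replication. It puts relapse at about 10%, and the Discussion describes NMDA receptor antibody encephalitis as a late complication. The Trial closure section lets the steering committee stop the trial on the data monitoring committee's advice, and that advice depends on events reaching the unit in good time.

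**Working it through.** The article gives no figure for reporting delay, so there is none to reproduce. The check is to take the stated deadlines and work out how late an event may arrive.

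**Inputs (Pharmacovigilance section), with randomisation as day 0**

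- End of 24-hour reporting: day 30.
- 26-week point: 26 × 7 = day 182. Form due 4 weeks later: 182 + 28 = day 210.
- 78-week point: 78 × 7 = day 546. Form due 6 weeks later: 546 + 42 = day 588.
- Notification limits: 7 days (fatal or life-threatening, from notification) and 15 days (others).

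**Formula:** longest permitted lag = form deadline − day of event, where the event is recorded on the next scheduled form.

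| Event | Next form due | Longest permitted lag |
|---|---|---|
| Day 31 | Day 210 | 210 − 31 = 179 days |
| Day 182 (week 26) | Day 210 | 210 − 182 = 28 days |
| Day 183 (just after week 26) | Day 588 | 588 − 183 = 405 days |
| Day 546 (week 78) | Day 588 | 588 − 546 = 42 days |

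Even an event on the day of a visit may arrive later than 7 or 15 days after it happened. The part of follow-up with no prompt route described is (546 − 30) / 546 = 516 / 546 = 94.5%.

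**Does the 7-day return rule shorten this?** No. It runs from completion of the form, not from the event, and the safety forms in question are tied to the 26- and 78-week points.

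**Are the notification limits missed?** For fatal and life-threatening SUSARs the limit is counted from notification. With event on day *e* and receipt on day *r*, the limit falls on day *r* + 7. A long *r* − *e* moves the start of the clock but does not break the limit. For an event on day 31 received on day 210, the limit falls on day 217, which is 217 − 31 = 186 days after the event. The promise is kept in form but gives little protection.

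**Causality of a death, up to day 30**

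| Step | Who decides, as written |
|---|---|
| Whether 24-hour reporting applies | Site investigator, by suspicion |
| Causality of adverse events in general | Site investigator or designee |
| Causality of a death | Steering committee |

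The first two rows agree with each other. The third does not fit them unless the committee's review comes on top of the site's. The section does not say so, and gives no time for it.

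**The case against.** Several stronger readings are tempting, and the article does not support them.

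- *Deaths escape 24-hour reporting.* Not all do. Up to day 30, a death that the investigator suspects is related falls inside the rule. Since a SUSAR requires suspicion, a fatal one in that window can start its clock at once.
- *The 7- and 15-day limits are defeated.* The 7-day limit runs from notification, so late receipt delays it and does not breach it.
- *A fatal reaction may wait a year for the committee.* At least annually is a minimum for general oversight meetings. Nothing says that a death waits for a scheduled meeting, and nothing excludes an ad hoc review.
- *About nine deaths fall under the exemption.* The Sample size section expects about 10% of patients to die before the primary outcome; 10% of 90 is 9. That is the total to week 26. The exemption concerns only unsuspected deaths up to day 30, and the article gives no split by time or by suspicion, so their number cannot be derived.

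The design also has a fair defence. Treatment lasts 4 days, viral clearance is checked at 2 weeks, and a 30-day intensive window runs well past the last dose. The trials unit is in regular contact with sites, and the data monitoring committee sees unblinded grouped data throughout. So the lags above are the longest permitted, not the expected ones. The article is also condensed, and the full protocol may hold an expedited route for late suspected reactions.

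What remains is that the article does more than leave out detail. It states a specific route for late SAEs and a duty covering the whole study, and the route does not serve the duty. Regular contact with sites and access to grouped data do not require a site to report a late suspected reaction promptly. A short treatment makes late reactions less likely, but the article itself extends the duty beyond day 30.

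**Conclusion.** The concern holds in a limited form. After day 30 the section describes no prompt route for a suspected related SAE, fatal or not, although all SUSARs during the study are to be notified. The permitted delay to the trials unit is up to 179 days for an event on day 31 and about 405 days for one just after week 26. The consequence is a late start to the notification clock and a late view for the data monitoring committee. It is not a formal breach of the 7-day limit.

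Separately, the section does not reconcile the site investigator's role in judging causality with the steering committee's role for deaths. This does not mean that deaths in general go unreported, and no count of exempted deaths can be given.

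The lags assume that time is counted from randomisation, that a late event is recorded on the next scheduled form, and that the form arrives on its last permitted day. The conclusion would fall away if the full protocol, which is not shown, already has an expedited route for late suspected reactions and defines the two causality roles. In that case only the article's wording needs correcting.

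**What to change.** Reconcile the statements within the Pharmacovigilance section in three respects:

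1. Any SAE, including death, that the site investigator suspects is related to the study drug goes to the trials unit on the expedited route throughout the 78-week follow-up, not only to day 30.
2. The site investigator's causality assessment triggers reporting. Steering committee review of deaths is additional and does not delay notification.
3. SAEs after day 30 that are judged unrelated can stay on the 26- and 78-week forms.

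The cost is a short protocol amendment, a notice to sites and a few extra SAE forms. Sample size, the primary outcome and its analysis are untouched. If the full protocol already contains these rules, a clarifying sentence is enough.

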### Patient and public involvement

The Encephalitis Society was consulted and provided advice on the design of the trial and the difficulties participants and their families encounter. The chief investigator of the DexEnceph study is the President of the Encephalitis Society. The chief executive of The Encephalitis Society is a coapplicant on the grant application and a coauthor on this paper.

The Encephalitis Society has also provided patient representatives at our trial steering committee and assisted in the production and dissemination of trial promotional materials.

The Encephalitis Society will support publication and dissemination of the trial findings among lay, therapeutic and health professionals through the use of web materials, newsletters and guides as well as at conferences and seminars. All patients and their family/carers will be acknowledged in any outputs from the trial. We also work with The Encephalitis Society on a programme of teaching events and produce guides for healthcare professionals and lay people.

In instances where trial participants and their families have ongoing difficulties the central study team seek help for them through the Encephalitis Society and appropriate specialists for further assistance.

### Ethics and dissemination

The trial falls within the remit of the EU Directive 2001/20/EC, transposed into UK law as the UK Statutory Instrument 2004 No 1031: Medicines for Human Use (Clinical Trials) Regulations 2004 as amended. This trial is registered with the Medicines and Healthcare products Regulatory Agency (MHRA) and granted Clinical Trial Authorisation (CTA). The EUDRACT number for CTA reference is 2015-001609-16. Ethical approval has been obtained from a multicentre research ethics committee familiar with the principals of the Mental Capacity Act 2005 guidance for sites in England and Wales and the Adults with Incapacity Act 2008 for sites in Scotland as the principals are relevant to a clinical trial of investigational medicinal products (CTIMP). Clinical Research Governance approval was given through the Sponsor, The University of Liverpool. The trial protocol was approved by a National Research Ethics Service Committee reference is 2015-001609-16 (Attained 31 March 2016) and underwent independent review at the Research and Development offices at participating sites. This study abides by the principles of the World Medical Association Declaration of Helsinki (1964) and Tokyo (1975), Venice (1983), Hong Kong (1989) and South Africa (1996). Due to the nature of this trial it also abides by the Medicine for Human Use (Clinical Trials) regulations 2004 (S.I.2004:1031) and all following amendments which are incorporated into UK law.

### Informed consent process

In obtaining and documenting informed consent, the investigators adhere to National Institute for Health Research (NIHR) Good Clinical Practice guidelines and the ethical principles derived from the Declaration of Helsinki. Staff delegated by the principal investigator and appropriately trained with experience in obtaining informed consent, discuss the objectives, risks and inconveniences of the trial and the conditions under which it is to be conducted with the patient or if the patient lacks capacity with a legal or professional representative. Trial information documents and points of contact for further information are provided and the potential participants are given adequate time to consider their decision(online supplemental file 2).

10.1136/bmjopen-2020-041808.supp2Supplementary data

As this is a CTIMP, the clinical trial regulations for incapacitated adults are followed (Medicines for Human Use Clinical Trial Regulations 2004 and amendments). When a legal representative has given consent for a patient to participate in the trial and the patient subsequently regains capacity, the research team will provide the patient information sheet and request consent from the participant. Patients are allowed to withdraw from the study at any point and may request withdrawal of their data collected until this point. Prospective consent can also be obtained prior to a positive PCR result so participants may have adequate time for contemplation.

As suspected encephalitis is a medical emergency, a deferred consent process is used for the collection and retention of some samples as part of routine clinical management. Using emergency deferred consent for samples involves taking additional samples of blood and CSF only if the procedure is being performed for clinical care. If deferred consent has been used, written consent is requested from either the patient or a legal representative as soon as is possible and appropriate, with samples discarded if this is declined. This approach is based on discussions with patients and the public through the Encephalitis Society.

### Data capture methods

Data are stored securely in line with the Data Protection Act 1998. The randomisation system, data capture form and CRF have been designed to optimally protect participant information and to maintain confidentiality. Trial data are captured at local sites using paper CRFs. These are then sent into the clinical trials research unit for data entry into the study-specific database. Completed CRFs are returned to clinical trial research centre within 7 days of completion. A copy of the CRF sent over to the clinical trials research unit is retained at site. CRFs and consent forms are stored separately and securely at all times in dedicated areas of the clinical trials research unit.

CRFs are checked for data quality by the clinical trials research unit in Liverpool responsible for ensuring data collection and storage.

Patients’ anonymised and labelled neuroimaging data are put on to discs at site and sent to the clinical trials research unit; the images can also be transferred via the Image Exchange Portal in an encrypted manner. The final dataset will be solely accessible to the central study team at the University of Liverpool for analysis and write up.

### Dissemination

The results of the DexEnceph trial will be published in a high impact journal in a timely manner to present the findings to front-line clinicians. They will be presented at the annual conference organised by the Encephalitis Society and at other meetings. Authorship of the final papers will be determined in accordance with the international committee of medical journal editors’ guidelines. The investigators will be involved in the preparation and drafting of the manuscripts. There is no intended use of professional writers.

## Discussion

This protocol describes the design of a randomised controlled trial to examine the role of dexamethasone in the management of patients with HSV encephalitis. HSV encephalitis is a rare sporadic acute disease, and the trial has been designed to take this challenge into account, along with the practicalities of running the trial in a UK National Health Service setting. In particular lessons were learnt from a previous similar European study, the GACHE trial, which was stopped early because of recruitment difficulties. Recruitment to the GACHE trial necessitated patients had focal neurological signs of no longer than 5 days prior to admission, while DexEnceph has less stringent criteria and reflects the diverse ways in which HSV encephalitis may present. DexEnceph has been designed to be both practical and pragmatic, in that patients must be recruited within 7 days of the PCR result becoming available. This allows for occasions where it may take longer to get the PCR performed, and also allows time for patients admitted to district general hospitals, which may not be study centres, to be transferred to larger hospitals which are. DexEnceph also has the advantage in that its recruitment projections were based on preliminary data garnered from the ENCEPH-UK NIHR programme (www.encephuk.org) and from a multicentre cohort study of encephalitis in England, run by the Health Protection Agency (fore-runner to the Health Protection Agency).^9^ These two studies provided direct information on the number of HSV encephalitis patients presenting to UK hospitals. The GACHE study was a double-blind placebo controlled study. Our choice of an open-label observer-blind study, avoided the logistic challenges of ensuring blinded study drug was available across the large number of centres, which might each see only one to two patients per year. We are confident our robust monitoring and trial promotion ensures the majority of eligible patients are recruited. NMDA receptor antibody encephalitis (which is treated with corticosteroids and other immunomodulatory therapies) is being recognised increasingly as a late complication of HSV encephalitis.^47 48^ DexEnceph may also be able examine whether corticosteroids reduce the incidence of this complication. If there is demonstrable efficacy of corticosteroid in improving neuropsychological, imaging and quality of life outcomes, without compromising patient safety the results will be far reaching.

### Collaboration with France

Because we recognised from the start that there may be difficulties keeping to recruitment targets in the DexEnceph study, we worked with colleagues in France to develop a parallel French study (DexEnceph-France). This follows the UK DexEnceph protocol as closely as possible, while being pragmatic about the constraints of a different country’s healthcare system. The French trial is based in 10 hospitals with the lead centre being Grenoble Alpes University Hospital and the aim of recruiting 30 patients.

The intention is for the two trials to be analysed separately, with the option of also combining them into an overall analysis which will give additional power to detect a treatment effect.

### Trial status

The trial was opened in the UK in August 2016. By June 2019 it was running at 45 NHS trusts, and

by Feburary 2020 71 patients had been randomised. However, in March 2020 recruitment to the trial was paused, along with most other NIHR-funded studies, because of the Covid-19 pandemic. However ongoing assessment was completed for patients in the study, and the primary outcome was not missed for a single such patient. Conducting such assessments despite social distancing requirements required some ingenuity on the part of the neuropsychology team. Recuitment to the study reopened in June 2020 (one of the first non-Covid-19 studies to do so) and by June 2021 had recruited 82 (91%) of the target 90 patients. The progress of the trial through the pandemic is a testament to the committment of the research teams around the country, as well as the patients and their families. The trial is currently expected to complete recruitment in January 2022, and to complete followu up for the primary outcome 6 months later. The research team have used the lessons learnt in conducting a randomised controlled acute treatment trial of this rare disease to apply succesfully for funding to study the role of intravenous immunoglobulin (IVIG) in autoimmune encephalitis. If you are interested in seeing whether your hospital could become involved in the Enceph-IG study please visit www.liverpool.ac.uk/encephig, or email: [contact]
